**Figure 5: Timeline for the treatment regime for UPA and LNG-IUS, and study assessments (Prior to USM)**

[figure not shown]

**Key:** EB endometrial biopsy; FU patient questionnaire

### 7.3 OUTCOMES COLLECTED AT STUDY ASSESSMENTS

Table 1 shows the outcomes collected at each time point in the UCON trial and mechanistic sub-study.

**Table 1: Schedule of outcome assessment for UCON trial and mechanistic studies**

(X) optional ((X)) dependent upon endometrial assessment at previous time point

| Timepoint                                                                                                                                          | Screening
(1) | Baseline
(2) | 3 months
(approx)
(3) | 6 months
(approx)
(4) | 12
months
(approx)
(5) | Post-
treatment
1 (6) | Post-
treatment
2 (7) |
|----------------------------------------------------------------------------------------------------------------------------------------------------|------------------|-----------------|-----------------------------|-----------------------------|---------------------------------|-----------------------------|-----------------------------|
| Written informed consent                                                                                                                           | X                |                 |                             |                             |                                 |                             |                             |
| Patient questionnaires (MMAS, UFS-QOL, EQ-5D-5L, ICE-CAP, SAQ)                                                                                     |                  | X               | X                           | X                           | X                               |                             |                             |
| Other patient reported outcomes (compliance, adverse events, willingness to recommend to a friend, rating of treatment, satisfaction of treatment) |                  |                 |                             |                             | X                               |                             |                             |
| Menstrual bleeding diary                                                                                                                           | X                |                 | X                           | X                           | X                               |                             |                             |
| Blood sample, to observe haemoglobin and oestradiol levels (not safety bloods)                                                                     | X                |                 |                             |                             | X                               |                             |                             |
| Ultrasound pelvic assessment                                                                                                                       | X                |                 |                             |                             | X                               |                             |                             |
| Endometrial biopsy                                                                                                                                 | X                |                 |                             |                             | X UPA only **                   |                             |                             |
| Endometrial biopsy – additional for women in UPA group who exhibit PAEC                                                                            |                  |                 |                             |                             |                                 | ((X)) UPA only              | ((X)) UPA only              |
| Follow up outpatient appointment to discuss post-trial treatment options                                                                           |                  |                 |                             |                             |                                 | (X) UPA only                |                             |
| Liver Function Test (if indicated)                                                                                                                 |                  |                 | X***                        |                             |                                 |                             |                             |
| Purposive samples 1 and 2 (Edinburgh sub-study only)                                                                                        |                  |                 |                             |                             |                                 |                             |                             |
| Endometrial biopsy and blood test                                                                                                                  | X                |                 |                             | X UPA only                  | X UPA only                      | ((X)) UPA only              | ((X)) UPA only              |
| MRI (DCE-MRI and high resolution structural MRI)                                                                                                   |                  | X               |                             | X UPA only                  | X UPA (+) only                  |                             |                             |

(X) optional ((X)) dependent upon endometrial assessment at previous time point

(+) MRI to be performed in final week of treatment

\* Endometrial biopsies will be stored at the University of Edinburgh Female Reproductive Tract Tissue Resource (10/S1402/59) and 16/ES/0007.

\*\* An end of study endometrial biopsy for women discontinuing UPA treatment should be arranged four weeks post cessation.

\*\*\* As per the Urgent Safety Measure: LFTs will be performed monthly during the 12 week treatment period for women currently taking UPA. A LFT must also be performed 2-4 weeks after the final dose of UPA. LFTs must include transaminases (ALT and AST). LFT results must be recorded on the UCON trial database.

## 8 DATA COLLECTION

### 8.1 DATA COLLECTION FORMS

Data for the purpose of assessing the efficacy and safety within the UCON trial will be collected from the women, her gynaecologist and the histopathologist on a number of data collection (case report) forms.

#### 8.1.1 Participant Questionnaire

The participant questionnaire is a booklet containing a number of validated instruments and questions completely independently by the participant. The booklet at baseline will contain:

- Menorrhagia Multi-Attribute Scale (MMAS)
- Uterine Fibroid Symptom and Quality of Life (UFS-QoL)
- Quality of Life (EuroQoL EQ-5D-5L) and (ICECAP-A)
- Sexual Activity Questionnaire (SAQ) Cycle regularity and duration
- Visual analogue scales (0-10) for pelvic pain during periods, intercourse and at other times

At the three follow-up timepoints, the following additional data will be sought:

- Adherence to UPA dosing schedule, as subjectively reported on an ordinal scale by the participant (for those allocated to UPA).
- Adherence to LNG-IUS for those allocated this group.
- Discontinuation or changes in allocated treatment.
- Any hospitalisations, or further investigations or treatments from a gynaecologist.
- Any pregnancies.
- Serious adverse events reported by participants, principally those that are unexpected or are known and relevant to the trial treatments.

The booklet will either be sent out in paper form by post, be emailed as a data-form enabled attachment, be via a password protected web form or be presented to the woman in an outpatient clinic. Various ways in which to contact women (land line and mobile telephone, email, address) will be collected and all may be used in the process of collecting the data.

#### 8.1.2 Menstrual Diary

The standard pictorial blood assessment chart (PBAC) (14) will be given to the woman at the first clinic visit to allow her to complete during her next menstruation and return it at the second clinic visit, which should be scheduled to be at least 4 weeks after the first.

Both UPA and LNG-IUS may induce amenorrhea (absence of bleeding) in some women, so whilst on treatment, the concept of a regular cycle is problematic. A modified menstrual diary, with ordinal questions regarding bleeding each day, will be used to establish the degree of menstrual bleeding. This will be completed for 28 days from week 8 for women in the LNG-IUS group and for 56 days

from week 8 in the UPA group, then again at week 24 and week 40, for 28 and 56 days for the LNG-IUS and UPA groups, respectively.

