### **2.2.2 Secondary outcomes**

- Menstrual bleeding will be captured by validated Pictorial Blood Loss Assessment Chart (PBAC) (20). The standard PBAC is a validated and well used assessment of menstrual blood loss in women. It will be used to generate the incidence of amenorrhoea, light, normal and heavy menstrual bleeding. It will also be used to ascertain the number of days bleeding per month.
- Cycle regularity and duration.
- Visual analogue scales (0-10) for pelvic pain during periods, intercourse and at other times
- Uterine Fibroid Symptom and Quality of Life (UFS-QoL) instrument, which contains a health related quality of life (HRQoL) domain and a symptom domain (21). Sexual Activity Questionnaire (22), a measure of sexual functioning, used in other HMB trials (9). The sexual activity questionnaire is a valid, reliable and acceptable measure for describing the sexual functioning of women in terms of pleasure and discomfort. It is quick and easy to administer and has good face validity delineating between the sexual functioning of pre and post-menopausal women.

- General quality of life questionnaires - EuroQoL-5D (EQ-5D-5L) (23) and ICECAP-A (24).
- Satisfaction with treatment outcome measured on a 5-point Likert scale.
- Participant rating of effect of treatment on HMB over 12 months measured on a 4-point Likert scale.
- Whether participant is willing to recommend the treatment to a friend.
- Surgical intervention (hysterectomy, endometrial ablation and other gynaecological surgery)
- Adherence to trial treatments and reasons for changing treatment, as reported by the participant.
- Serious adverse events and reactions reported by participants, principally those that are serious and detailed in the respective Summary of Product Characteristics (SmPC) and those that are unexpected.
- Clinical measurements via pelvic ultrasound: uterine volume, evidence of adenomyosis, presence of fibroids, largest fibroid volume, endometrial thickness, endometrial appearance (regular/irregular), evidence of ovarian cysts.
- Clinical measurement via endometrial biopsy: primary diagnosis (normal/benign/hyperplasia/malignant) and further sub-diagnoses if non-normal.
- Clinical measurement via blood samples: serum haemoglobin and oestradiol levels.

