### **9.2.2 Secondary analysis**

MMAS scores at three and six months follow-up will be analysed as per the primary analysis. Data from the other continuous measures (UFS-QOL, EQ-5D, ICE-CAP, VAS and SAQ) will be analysed in a similar fashion to the MMAS scores. Further exploratory analysis using a repeated measures model will also be used for these continuous measures to examine differences over all time-points. Bleeding diary scores will be converted into categories including the proportion with amenorrhoea ( $=0$ ) and heavy bleeding ( $\geq 100$ ). They will be analysed using relative risks and chi-squared tests. Time from randomisation to surgery (hysterectomy or endometrial ablation) will be analysed by log-rank test with a Cox Proportional Hazard (PH) model also built if the assumptions of proportionality are met. Other outcome measures (Likert responses, Likert ordinal responses, satisfaction) will be analysed using standard methods (tests for trend, absolute and relative risks). Paired t-tests will be used to examine differences within groups over time.

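### The follow-up heavy-bleeding category (score of 100 or more) cannot be derived from the unscored modified diary, and section 9.2.2 does not say which UPA diary days are scored

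*Protocol*

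**What the plan says.** **Outcome definition (section 2.2.2).** The PBAC is named as the instrument for menstrual bleeding: "It will be used to generate the incidence of amenorrhoea, light, normal and heavy menstrual bleeding". No cut-offs are given there.

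**Collection (section 8.1.2).** Before treatment: "The standard pictorial blood assessment chart (PBAC) (14) will be given to the woman at the first clinic visit". On treatment the section says that a regular cycle is a problematic concept, and substitutes another form: "A modified menstrual diary, with ordinal questions regarding bleeding each day, will be used to establish the degree of menstrual bleeding". Its length differs by arm: "This will be completed for 28 days from week 8 for women in the LNG-IUS group and for 56 days" from the same week in the UPA group, "then again at week 24 and week 40, for 28 and 56 days for the LNG-IUS and UPA groups, respectively".

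**Timing (section 7.2, item 2).** Both arms keep the diary over the last four weeks of a UPA course or the equivalent time for LNG-IUS. The UPA group adds the first four weeks off drug.

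**Analysis (section 9.2.2).** "Bleeding diary scores will be converted into categories including the proportion with amenorrhoea", set at 0, and heavy bleeding, set at 100 or more. Then: "They will be analysed using relative risks and chi-squared tests". The section names neither the instrument, nor a scoring rule, nor the days that count.

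**The concern.** Three sections describe one outcome and do not fit together. A cut-off of 100 needs a points total. Section 2.2.2 points to the PBAC for the categories, but the follow-up data come from a different diary with ordinal daily answers and no stated points. As written, the rule for heavy bleeding has nothing to act on after baseline.

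The second gap is the scoring window. One arm returns twice as many diary days as the other, and the extra days fall where a withdrawal bleed may occur or is expected (section 6.2.1). A fixed cut-off applied to everything returned would treat the arms differently.

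Menstrual blood loss is the first outcome listed in the between-arm secondary objective, at 3, 6 and 12 months (section 2.1.2). What is at stake is the interpretation of that secondary result.

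**Working it through.** There is no sample-size or power figure to reproduce on this point. The check sets the sections side by side and counts days.

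**1. Can the cut-offs be applied?**

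- Baseline: standard PBAC (8.1.2), so the PBAC cut-offs can be used.
- Follow-up: modified diary with ordinal daily answers (8.1.2). The protocol gives no score, range or conversion to PBAC points.
- Score of 100 or more: cannot be derived at follow-up from what is stated.
- Score of 0: derivable if the diary has a no-bleeding level. This is an assumption, because the form is not shown.

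**2. Which days does each arm supply?** Under the regime before the urgent safety measure (6.2.1), three courses of 12 weeks on and 4 weeks off give treatment weeks 0–12, 16–28 and 32–44. A diary starting at week *w* covers *w* to *w*+4 for LNG-IUS and *w* to *w*+8 for UPA.

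| Start | LNG-IUS | UPA, scheduled on drug | UPA, scheduled off drug |
|---|---|---|---|
| Week 8 | 8–12 | 8–12 (28 days) | 12–16 (28 days) |
| Week 24 | 24–28 | 24–28 (28 days) | 28–32 (28 days) |
| Week 40 | 40–44 | 40–44 (28 days) | 44–48 (28 days) |

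At each time point the first 28 UPA days coincide with all 28 LNG-IUS days. This counts both arms from a common week 0 and ignores the ±5-day tolerance in the regime. A like-for-like window therefore exists, and section 9.2.2 does not name it.

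**3. What would happen if all 56 UPA days were scored?** Suppose daily scores are non-negative and summed.

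- Length ratio: 56/28 = 2.
- Average per 28 days that reaches the threshold: 100/2 = 50 for UPA, against 100 for LNG-IUS.
- A woman scores 0 over 56 days only if she scores 0 in both halves. The share at zero can therefore only stay level or fall, and the share at 100 or more can only stay level or rise.

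As an illustration, take 70% at zero on drug. Section 1.1 reports amenorrhoea in over 70% in two earlier fibroid trials; its use here is an assumption. Let the share at zero off drug run from 0% to 70%, also an assumption. If the halves were independent, the 56-day share would be 0.70 × 0 = 0% to 0.70 × 0.70 = 49%. Its upper limit under any dependence is the smaller of the two shares, so 0% to 70%. The matched 28-day figure would be 70%.

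**4. After the urgent safety measure.** No new UPA courses start (5.6.1, Change of Treatment following USM). Section 7.2 item 1 was adapted so that women who stop complete questionnaires as first scheduled. Item 2, on the diary, was not. For women who stopped, weeks 24 and 40 need not be on-drug weeks, so the comparison window has to be defined by calendar week.

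**The case against.** The strongest reply is that the unequal lengths are deliberate and already explained. Section 7.2 matches four weeks in both arms and adds a separate off-drug period for UPA. Nothing says that the 56 days are pooled. A reader might infer from 56 against 28 days that the arms are not comparable; the protocol does not support that, because matched data are scheduled at every time point. Naming the window is also something a SAP often does, and section 9.2 promises one that was not available here.

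A reader might also infer that no bleeding category can be derived. That goes too far, since amenorrhoea probably can be. Section 9.2.2 speaks of diary scores and does not itself call them PBAC scores; the link comes from section 2.2.2.

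Finally, an unadjusted relative risk with a chi-squared test is valid. Ignoring the minimisation factors generally costs efficiency, and no bias has been shown. Baseline PBAC may be missing for some women, because section 5.4 collects the diary only if a period fell between visits.

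All of this stands, and it narrows the point. It does not remove the conflict: the protocol names one instrument, collects follow-up on another, and fixes a threshold with no stated meaning on the second.

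**Conclusion.** The point holds in a limited form. The heavy-bleeding category at follow-up cannot be derived from what the protocol states, and the days to be scored are not named.

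The size of any distortion depends on a choice that the protocol leaves open. If the matched 28 days are used, the unequal lengths cause none. If all 56 UPA days were summed against the fixed cut-offs, the effective heavy-bleeding threshold for UPA would halve to 50 per 28 days and UPA amenorrhoea could only be understated. No numerical bias can be given, because the protocol states no withdrawal-bleed rate; the range in the working is illustrative. The conclusion assumes that no scoring rule is printed on the diary form, which is not shown.

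Lack of adjustment is an opportunity for a better estimate, not an error. The issue concerns one secondary outcome, and the primary MMAS analysis is untouched.

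**What to change.** 1. In section 9.2.2, define the follow-up bleeding categories on the modified diary's own levels, or give an explicit conversion, and drop the bare rule of 100 or more. Correct section 2.2.2 so that it names the instrument actually used at follow-up.
2. Make the between-arm comparison on the same 28 calendar days in both arms (weeks 8–12, 24–28 and 40–44), by intention to treat and including women who stopped UPA. Report the second 28 UPA days as a separate, labelled result.
3. Estimate relative risks from a model adjusting for the minimisation variables, for example Poisson regression with robust errors. Add baseline PBAC where it is available, and state how missing values are handled.

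Do not re-issue the PBAC at follow-up. With recruitment suspended, that would split participants between two instruments, and section 8.1.2 gives a reason for not using a cycle-based chart on treatment.

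The cost is wording and some extra programming. Site categories may be sparse in the adjusted model, so a rule for combining small sites should be set in advance. No new data collection is needed.

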### **8.1.3 Clinical Assessment and Randomisation Form**

At the first clinic visit, the gynaecological clinical history of the woman will be taken and details of duration of HMB symptoms, previous gynaecological treatment for HMB, and the contraceptive use and needs of the woman will be collected alongside basic demographic details. A blood sample to observe serum haemoglobin and oestradiol levels will be taken and results recorded in the clinical assessment and randomisation form.

### **8.1.4 Ultrasound Form**

A pelvic examination by transabdominal and/or transvaginal ultrasound will be undertaken and cardinal features noted as possible presence of fibroids and uterine size and size of largest fibroid to make the comparison between baseline and 12 month follow-up possible.

### **8.1.5 Clinical Assessment and Randomisation Form and Screening Logs**

The Clinical assessment and Randomisation Form is a checklist for eligibility and key prognostic details needed for minimisation within the randomisation. The Clinical assessment and Randomisation Form is completed by the investigator or UCON research nurse before randomisation.

The Screening Logs, described in Section 5.5, will record basic details of all women approached, including those who are found to be ineligible and those that decline to participate. This should be kept up to date by the UCON research nurse.

### **8.1.6 Endometrial Biopsy Report Form**

The local consultant histopathologist will report on the morphology and cellular architecture of the endometrial biopsy sample on a local report form. The baseline biopsy and the 48 week post treatment biopsy in the UPA group will be assessed using standard techniques to identify PAECs. Independent analysis of the slides taken from the endometrial samples by the Lead Pathologist at the University of Edinburgh will be recorded on a standardised report form.

### **8.1.7 End of Study Visit Form**

The research nurse will contact each participant to arrange their end of study visit (follow-up assessment) which will ideally take place between approximately weeks 49 and 57. The assessment will include confirmation of whether there was a change to treatment during trial participation, satisfaction with treatment, participant rating of treatment and whether they would recommend to a friend and onward treatment intention.

Participants in the LNG-IUS group will undergo an ultrasound and have a blood sample taken. Participants in the UPA group will undergo an ultrasound, endometrial biopsy and have a blood sample taken.

For participants in the UPA mechanistic sub-study will undergo an ultrasound, endometrial biopsy, MRI scan and have a blood sample taken.

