## **6.2 DOSE AND DELIVERY OF IMPS**

### **6.2.1 UPA**

**Randomisation was suspended on 12 February 2018 on account of a USM requirement from the MHRA (12th February 2018).**

**Participants already randomised to receive UPA may complete their current 12 week course No further courses will be initiated.**

**[Procedure adopted prior to USM:** Those allocated to UPA will receive proprietary ulipristal acetate 5mg, orally, once daily.

A single tablet must be taken orally once daily with or without food, at approximately/ or as close as possible to the same time each day. The participant should start taking UPA within the first five days of starting their menstrual bleeding.

If a participant misses a dose, she should take UPA as soon as possible. If the dose was missed by more than 12 hours, the participant should not take the missed dose and simply resume the usual dosing schedule.

Women will be instructed to take UPA in 3 courses according to the following cyclical regime ( $\pm$  5 days):

1. One 5mg tablet of UPA to be taken daily for 12 weeks then stopped for 4 weeks, when light vaginal bleeding may occur (withdrawal bleed).
2. After 4 weeks off treatment, regardless of whether they experience a withdrawal bleed, they should recommence UPA 5mg daily for another 12 weeks, then stop for 4 weeks, when they will expect to have a withdrawal bleed.
3. Repeat as for treatment courses (2).

We have chosen this regime as women and their clinicians will likely prefer a regime that has only one menstrual bleed between treatment courses and thus our study will be able to provide valuable data on this aspect of UPA treatment. ]

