## **7.2 TIMING OF STUDY ASSESSMENTS**

The overriding principles for the timing of the follow-up study assessments are:

1. The patient completed questionnaires should ideally be completed in the final week of each on-treatment cycle or equivalent for the UPA group, and at an equivalent time for the LNG-IUS group. Participants who stop treatment should complete questionnaires as originally scheduled (i.e. approximately 3, 6 and 12 months post randomisation).
2. The menstrual blood loss diary whilst on treatment should ideally be completed over the final four weeks of each treatment cycle in the UPA group, and at an equivalent time for the LNG-IUS group. The UPA group will also be asked to complete the diary during the first 4 weeks off treatment before the start of the next treatment cycle (as per the cyclical regime stated in section 6.2.1).
3. The post-treatment endometrial biopsy should be completed after 4 weeks off treatment, which would be approximately 48 weeks after UPA was commenced.
4. Should PAECs be observed in the post-treatment biopsy specimen in the UPA group, a repeat endometrial biopsy should be taken around 13 weeks after the completion of treatment, and then again around 26 weeks post-treatment if PAECs persist.
5. The endometrial biopsy, blood sample and MRI at time point 26 weeks in the sub-study should be in the final week of the second UPA cycle, to determine the features of the endometrium while receiving treatment.

A timeline for the treatment regimens and completion of the assessments is shown in Figure 4.

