### 8.5.2 Uterine and fibroid function

The aim of the MRI sub-study is to investigate the hypothesis that UPA will reduce blood flow and blood volume in the endometrium and myometrium in women with HMB. In particular, dynamic contrast enhanced MRI (DCE-MRI) and high spatial resolution structural MRI will be obtained in a subgroup of 20 women treated with UPA. DCE-MRI, combined with pharmacokinetic modelling, yields quantitative estimates of physiological parameters, including tissue blood flow, blood volume fraction and endothelial permeability, as well as volume fraction of the extracellular extravascular space. Structural MRI provides high resolution images suitable for structural segmentation and radiological evaluation that, when combined with design based stereological analysis (20), yield accurate and precise measurements of uterine and fibroid volume for early assessment of treatment response.

Scanning will be performed at baseline, and at 6 and 12 months following commencement of treatment. Scans will take place during the secretory phase of the menstrual cycle at baseline and in the week prior to the end of the second and third cycles of UPA, weeks 27 and 43 respectively.

Structural images will be evaluated clinically by an experienced radiologist, and stereological analysis performed to determine the volumes of the uterus and of any fibroids. Modern design based stereological methods will measure total volume of endo- and myo-metrial compartments, and

volume, type and location of individual fibroids, with mathematically predicted precision, on high resolution MR images.

Dynamic Contrast Enhanced (DCE)-MRI will be used to measure uterine tissue perfusion. Contrast agent concentration is modelled as exchange between the blood plasma and extracellular interstitial spaces, providing maps of tissue blood flow, blood and interstitial volume fraction and artery to tissue delay (i.e. lag) time. DCE-MRI data will be analysed using the well-established adiabatic approximation to tissue homogeneity (AAHT) model, to generate pharmacokinetic maps of blood flow, blood volume and extracellular extravascular volume fraction; these will be used to extract representative values for endometrium, junctional zone, outer myometrium and fibroid tissue.

Both MRI approaches are novel in the context of SPRM administration, so will be piloted in the first patients, who may require repeat scans with a refined protocol.

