### 9.3 PROPOSED ANALYSES – MECHANISTIC STUDY

Outcomes for the n=20 prospectively studied women biopsied at 6 and 12 months will be compared to each participant's own baseline biopsy as a control. Outcomes (e.g. PH3 immunoscore changes within groups over time) will be analysed using paired t-tests following an appropriate transformation and also by using non-parametric methods (e.g. Wilcoxon signed rank test) for confirmation.

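### The last sub-study MRI is set on drug (week 43) in 8.5.2 and Table 1 but at the off-drug end-of-study visit (weeks 49-57) in 8.1.7, and 9.3 does not label samples as on or off drug

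*Protocol*

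**What the plan says.** All of this is in the protocol.

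- **Regimen (6.2.1, before the urgent safety measure):** "One 5mg tablet of UPA to be taken daily for 12 weeks then stopped for 4 weeks", given as three courses.
- **MRI timing in 8.5.2:** the follow-up scans are taken "in the week prior to the end of the second and third cycles of UPA, weeks 27 and 43 respectively". The same paragraph calls them 6- and 12-month scans: "Scanning will be performed at baseline, and at 6 and 12 months following commencement of treatment".
- **MRI timing in Table 1:** the 12-month MRI cell carries the footnote "MRI to be performed in final week of treatment".
- **MRI timing in 8.1.7:** the section describes an "end of study visit (follow-up assessment) which will ideally take place between approximately weeks 49 and 57" and closes its list of procedures with "For participants in the UPA mechanistic sub-study will undergo an ultrasound, endometrial biopsy, MRI scan and have a blood sample taken".
- **Biopsy timing in 7.2:** the 26-week sub-study biopsy, blood sample and MRI belong in the final week of the second course, expressly to see the endometrium under treatment. For the last biopsy, "The post-treatment endometrial biopsy should be completed after 4 weeks off treatment", at about week 48.
- **Analysis in 9.3:** women "prospectively studied women biopsied at 6 and 12 months will be compared" with their own baseline biopsy, by paired t-tests with a non-parametric check. The section does not say which sample is on drug and which is off, and it does not mention MRI.

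**The concern.** The MRI sub-study asks whether UPA lowers blood flow and blood volume in the uterus (2.1.3 and 8.5.2). That question needs a scan while the drug is being taken. The protocol expects the uterus to change once dosing stops: 6.6.2 says periods generally return within 4 weeks of the end of a course, and 6.6.1 (Endometrial changes) says the endometrial changes reverse. Section 8.5.2 also fixes the baseline scan in the secretory phase, whereas 8.1.7 names no cycle phase. A scan at the end-of-study visit could therefore differ from baseline through cycle timing as well as through drug withdrawal.

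The 12-month label adds to the risk. Week 43 is about 10 months, so someone scheduling by the label, or by the 8.1.7 list, would naturally book the scan with the other 12-month procedures.

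A smaller point concerns tissue. The 6-month biopsy is on drug and the 12-month biopsy is off drug, but 9.3 sets both against baseline in the same words. Without labels, a 12-month value close to baseline could be read as an effect that fades with longer use, when it may only show recovery after stopping.

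**Working it through.** **The plan's own figure.** Section 9.1.2 claims more than 90% power with 20 samples for a change above 1 SD in, for example, the PH3 immunoscore. I took 1 SD of the within-woman change, a paired t-test and two-sided 5%. The noncentrality is 1 × √20 = 4.47, and exact power is 98.9%. The normal approximation is Φ(4.47 − 1.96) = Φ(2.51) = 99.4%. The claim reproduces and is not in dispute. It concerns a tissue score, and no such figure is given for MRI.

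**Calendar.** Courses and breaks from 6.2.1, laid end to end from the first tablet:

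| Course | On drug | Off drug |
|---|---|---|
| 1 | weeks 1-12 | weeks 13-16 |
| 2 | weeks 17-28 | weeks 29-32 |
| 3 | weeks 33-44 | from week 45 |

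**Placing each assessment on it.**

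| Assessment | Source | Week | State |
|---|---|---|---|
| Second MRI | 8.5.2 | 27 | on drug |
| Third MRI | 8.5.2 and Table 1 footnote | 43 | on drug |
| Third MRI | 8.1.7 | 49-57 | off drug |
| 26-week biopsy | 7.2 | final week of course 2 | on drug |
| Post-treatment biopsy | 7.2 | about 48 | off drug |

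**Distances.**
- Between the two MRI rules: 49 − 43 = 6 weeks to 57 − 43 = 14 weeks.
- From the last tablet to the end-of-study visit: 49 − 44 = 5 weeks to 57 − 44 = 13 weeks.
- From the last tablet to the biopsy: 48 − 44 = 4 weeks.

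**Can scheduling tolerance close the gap?** The regimen allows ±5 days. If all three courses and both intervening breaks ran 5 days long, the last tablet would move by 5 × 5 = 25 days, which is less than the 5 weeks (35 days) to the earliest visit. The origin of the week count in 8.1.7 is not stated, but this does not rescue it. The same visit includes the endometrial biopsy, which 7.2 places after 4 weeks off treatment, so for a woman completing treatment the visit is off drug by its own contents.

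**Labels.** With 52 weeks to 12 months, week 27 is 27/52 × 12 = 6.2 months and week 43 is 43/52 × 12 = 9.9 months. The visit window is 49/52 × 12 = 11.3 to 57/52 × 12 = 13.2 months. The 12-month label fits the visit window, not week 43.

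**Size of the effect on the result.** To turn a mixture of on-drug and off-drug scans into a bias or a loss of power, three quantities are needed: the on-drug MRI change, the share of it remaining 5 to 13 weeks after stopping, and the share of scans taken late. The protocol gives none of them. Its closest figure is in 1.2, where PAECs fall from 62% to around 30% after one normal menstrual shedding. That shows that tissue off drug differs from tissue on drug, but it is a histological incidence and does not transfer to perfusion or to uterine and fibroid volume.

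**The case against.** **Two specific statements agree; one summary sentence does not.** Section 8.5.2 and the Table 1 footnote both give the on-drug week, and 8.1.7 is a description of a data form. The sub-study runs at one hospital with about 20 women, so a mixture of sites following different rules is unlikely. This limits the practical risk and points to which sentence should change. It does not remove the contradiction, since 8.1.7 says without qualification that the scan is done at that visit. The Edinburgh pathway and the assessment timeline are figures that are not shown, so they cannot be used to judge how clear the instructions were.

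**Recruitment to the sub-study is complete (5.4), and no new courses may start (5.6.1, Change of Treatment following USM).** Rewording 8.1.7 cannot move scans already taken. This stands, and it makes the analysis step the more useful part of the fix.

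**The off-drug biopsy is deliberate.** A reader might infer that the last biopsy is mistimed, or that 9.3 pools on-drug and off-drug tissue. Neither is supported. Sections 7.2 and 8.1.6 call it a post-treatment biopsy, its timing serves the PAEC follow-up, and 9.3 compares each time point with baseline without averaging them. Nor do the documents support making the 26-week sample the only test of the tissue objective. Section 2.1.3 includes tumour suppressors, and whether changes persist after three courses is a legitimate question. What remains is the labelling in 9.3.

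**Conclusion.** The MRI contradiction is literal and should be corrected. The two rules for the last scan are 6 to 14 weeks apart, do not overlap, and lie on either side of the last tablet. A scan made under 8.1.7 does not answer the on-treatment question in 8.5.2. This rests only on the regimen in 6.2.1 being followed to the end.

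For biopsies the point is one of labelling only. Both comparisons with baseline are sound if each is described as what it is.

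A reader might go further and infer a stated dilution, for example by carrying the 1 SD tissue effect over to MRI and assuming that it vanishes after withdrawal. The documents do not support this. The 1 SD refers to a tissue score, the reversibility statements concern the endometrium and not blood flow or fibroid volume, and the share of late scans is unknown. A reader might also infer that 9.3 prescribes the MRI comparison with baseline. It names biopsies only; the MRI comparison is inferred from the three-scan plan and the hypothesis in 8.5.2.

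The point affects the mechanistic sub-study and leaves the primary MMAS comparison untouched.

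**What to change.** 1. Reconcile 8.1.7 with 8.5.2 and Table 1. As two explicit statements place the scan on drug, remove the MRI from the end-of-study visit list in 8.1.7.
2. In 8.5.2 and Table 1, name the follow-up scans by week (27 and 43) instead of 6 and 12 months.
3. For every scan and biopsy, record the interval from the last UPA tablet. Treat a scan as on treatment only if it was taken before the course ended, and analyse scans taken after the last tablet separately.
4. In 9.3, keep both biopsy comparisons with baseline. Label the 6-month sample as on treatment and the 12-month sample as post-treatment (at least 4 weeks off drug), and report weeks since last tablet with the latter.

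The cost is wording in four places and the retrieval of last-tablet dates for about 20 women at one hospital, if these are not already held. No scan or biopsy is added and no comparison is given up. If some scans prove to be off drug, the on-treatment MRI analysis will rest on fewer than 20 women, and the report should say so.
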